**Figure 1 figure1:**
[figure not shown]
Scheduled further course of study.

### Research Staff

The research team consists of a doctoral student, several senior researchers, and a computer scientist employed at the Department of General Practice and Health Services Research of the University Hospital Heidelberg, Germany.

### Data Management

Data management is performed by the data management team of the Department of General Practice and Health Services Research of the University Hospital Heidelberg. The secondary data are collected by the control center of Ludwigshafen and are unrelated to the described questionnaire; they are governed by their own data management team.

Each data set is directly sent to and filed on a dedicated study server in the Department of General Practice and Health Services Research of the University Hospital Heidelberg. This also applies to the required secondary data transferred from the control center. Data access is granted only to the research staff directly involved in data collection and analysis. There will be no passing on of the unprocessed data to any external institution. Additionally, secondary data from the responsible control center will be linked and processed in the initial descriptive analysis. This descriptive analysis will form the basis for the variance analysis (see Data Analysis section). Working diagnoses will be converted to *International Classification of Diseases, Tenth Edition* codes by a research physician. The free-text entries will be analyzed separately with qualitative methods to obtain a deeper insight into patients’ motives for their behavior. Data storage and extraction will be performed with MySQL Community Server x64 (Oracle Corp).

### Data Analysis

The two main outcomes for our analyses are the number and percentage of inappropriate emergency calls and the reasons for patients being conveyed to a hospital without a medical indication. This total numbers will be further subdivided according to the paramedics’ assessments. Moreover, it is of interest if there are explanatory variables such as patient gender, patient age, operation area, and operation time in the data set that might be associated with inappropriate emergency calls or being conveyed to a hospital without a medical indication. This will be analyzed based on multivariable regression modeling [35]. To calculate frequencies, rates, and percentages, we will use the PROC SQL procedure in SAS (version 9.4, SAS Institute). To perform the multivariable analyses, we will use the PROC GENMOD procedure in SAS. For qualitative analyses, we will use MAXQDA (version 24.1, VERBI Software).

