**Methods:**

This will be an exploratory, noninterventional, cross-sectional study with a quantitative approach. The study is multicentric, with 21 ambulances in 12 different locations. The data for this study were collected via a questionnaire, newly developed for this study, for rescue personnel. Additionally, secondary data from the responsible control center will be linked and processed in an initial descriptive analysis. This descriptive analysis will form the basis for a subsequent variance analysis.

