**Conclusions:**

To our knowledge, this is the first observational study in which acute rescue operations are recorded on site. The focus of this study is on the trained paramedics’ assessment of whether rescue operations are necessary or not. Additionally, alternative treatments, such as out-of-hours care service or primary care service, are shown for each individual case. The study also intends to cover the question of which factors are relevant and statistically significantly connected to the misuse of ambulances.

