### Data Collection

During the 10-week period of data collection, access to the web-based questionnaire is available 24 hours a day, 7 days a week. The questionnaire is accessible via the link or QR code and can be filled in using a personal computer, tablet, or smartphone. The questionnaire website has been built exclusively for the study by the department conducting the study. The EMS personnel are encouraged to capture as many operations as possible during this period. The acquisition of the data sets is not bound to a certain time frame after the operations. Although the ambulance crew members must complete the questionnaire only after finishing an operation, the data sets only have to be completed within the period of data collection. The data set of each recorded ambulance operation is directly sent to a dedicated study server within the Department of General Practice and Health Services Research of the University Hospital Heidelberg via secure internet protocols. After closing of primary data collection, additional information and secondary data provided by the control center will be combined with each completely collected data set for interpretation. This comprises the time of day of the alert, the priority of the alert, the keywords of the alert, and a specific feedback code from the ambulance.

The scheduled course of the study is summarized in Figure 1.

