### Ethical Considerations

The ethics committee of the University of Heidelberg revised and approved this study on May 30, 2023 (S-250/2023). The trial has been developed and will be executed according to all relevant national and international rules and regulations under the Declaration of Helsinki (2013 version) and International Council for Harmonisation Good Clinical Practice (E6, R2) guidelines. Consent from all participants will be obtained in the web-based form, and access to the questionnaire will be granted only after approval. Protocol modifications are not scheduled and are not foreseeable; if the need for them arises, they will have to be approved by the ethics committee. In case of modifications, a new study protocol will be released to all study participants via an official email. Due to the anonymous collection of data, participants do not have the choice to opt out after completing the questionnaire. Furthermore, as the questionnaire is anonymous, there is no possibility of inferring the identity of the participant or any other personal information. There is also no way to identify the personal data of patients using the secondary operational data provided by the control center. There is no compensation, financial or otherwise, provided to participants.

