## Results

Data collection started as projected on September 18, 2023, and was ongoing until end of November 2023. We expect the documentation of several thousand rescue operations. We expect that many of these rescue operations will be unnecessary. Our intention is to train paramedics to give an immediate on-site evaluation of the correct care and treatment. We hope to identify patients’ reasons for calling a rescue coordination center so that we can give recommendations in advance on where to find the appropriate treatment options.

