## Discussion

To the best of our knowledge, this is the first observational study in which acute rescue operations are being recorded on site in Germany. This study was initiated to show how many inappropriate rescue operations, such as those for minor injuries or minor infections, take place in a defined study period. The assessment of these LACs is carried out directly on site by trained rescue personnel and not later in the clinic. The assessment is therefore supplementary and can provide information on operations without the need for a referral, which is a main strength of this study. Another focus is on a preclinical assessment to determine suitable, diverse alternatives to transport by ambulance to an ED for patient conditions that do not require urgent treatment.

One major intent of our study is to complement previous work, which includes several retrospective clinical evaluations and many qualitative studies, such as interview studies, on reasons for calling the EMS in LAC situations as seen through the eyes of patients, as well as of caregivers (mostly EMS personnel), and what circumstances encourage these calls [36-38]. It is known from previous data that around 30% to 35% of all rescue service operations transporting patients to the ED are rated as inadequate and unnecessary [5-8], so a similar proportion of operations with preferred alternative care methods is expected. Most of these inadequate EMS operations involve patients whose health conditions are assessed as being able to be adequately treated by a GP or in general outpatient care [6], which is why there may be a significant difference in the number of primary care–sensitive EMS operations depending on the general availability of and access to general practices and medical out-of-hours care [17]. Additionally, we anticipate that a certain number of transportation operations by ambulance for LACs will take place because of missing transportation alternatives, which has been found to be a relevant reason for ambulance misuse in previous work [39,40]. Previous studies have shown differences in the use of emergency services between urban and rural populations [41], as well as between groups with differences in relevant socioeconomic factors, such as age and personal mobility [42], which may be confirmed in this study.

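### No ambulance, station or crew identifier is among the listed data fields, so as specified the regression models cannot account for clustering of operations

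*Protocol article*

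**What the plan says.** The abstract's Methods paragraph describes the setting: "The study is multicentric, with 21 ambulances in 12 different locations". The Design section has one questionnaire completed per operation, reflecting the judgment of the best-qualified member of the crew. The Data Collection section urges personnel to record as many operations as they can over the 10 weeks, so the same raters contribute repeatedly.

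Table 1 lists the questionnaire items. They include a free-text operation number and a four-level class of operation area, but no ambulance, station, crew or rater. The Data Collection section then lists what the control center will add: "This comprises the time of day of the alert, the priority of the alert, the keywords of the alert", followed by a feedback code from the ambulance. No vehicle or station appears, and the article does not describe the feedback code as identifying a vehicle. The Ethical Considerations section adds that "as the questionnaire is anonymous, there is no possibility of inferring the identity of the participant".

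The Data Analysis section plans multivariable regression on gender, age, operation area and operation time: "To perform the multivariable analyses, we will use the PROC GENMOD procedure in SAS". It gives no correlation structure. The abstract's Conclusions state the ambition to learn "which factors are relevant and statistically significantly connected to the misuse of ambulances".

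**The concern.** The outcome is a judgment made on site. Crews may differ in how readily they call an operation inappropriate, and stations may differ in case mix and in local access to care. Either would make records from the same ambulance or station more alike than records from different ones. The Discussion allows that misclassification can arise from differing assessment standards, and the Design section postpones interrater reliability to a later roll-out.

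Positive within-cluster correlation has two consequences if it is ignored. Any interval for the main percentage is too narrow. Any test of a factor that varies mainly between stations rejects too often. Operation area is the plausible candidate: Table 2 assigns it by municipality, and the metropolitan class is essentially the core of one city. The article does not map stations to areas, so how closely area follows station is an inference.

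An analysis plan can choose the correlation structure later, but it cannot cluster on a variable that was never obtained. That makes this a gap in the data specification as well as a detail of the analysis.

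**Working it through.** **The plan's own figure.** The article states no sample size, interval, significance level or ICC, so there is nothing to reproduce.

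**Inputs from the article**
- Clusters: k = 21 ambulances or 12 locations (abstract, Methods; Setting).
- Proportion: the Discussion cites earlier data in which "around 30% to 35% of all rescue service operations transporting patients to the ED are rated as inadequate and unnecessary" and expects a similar share here. The midpoint, p = 0.325, is used.
- Number of records: the Results section says only "We expect the documentation of several thousand rescue operations".

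**Assumptions**
- N = 3,000, with 2,000 to 5,000 as the range.
- Equal cluster sizes.
- ICC of 0, 0.005, 0.02 or 0.05.

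**Step 1: half-width under independence.** 1.96 × √(0.325 × 0.675 / 3,000) = 0.0168, or 1.68 points.

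**Step 2: design effect.** DE = 1 + (m − 1) × ICC, with m = N/k. For ambulances m = 3,000/21 = 142.9; for stations m = 3,000/12 = 250. The clustered half-width is 1.68 × √DE.

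| ICC | DE, 21 clusters | Half-width (points) | DE, 12 clusters | Half-width (points) |
|---|---|---|---|---|
| 0 | 1.00 | 1.68 | 1.00 | 1.68 |
| 0.005 | 1.71 | 2.19 | 2.25 | 2.51 |
| 0.02 | 3.84 | 3.28 | 5.98 | 4.10 |
| 0.05 | 8.09 | 4.77 | 13.45 | 6.15 |

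At ICC 0.01, with N from 2,000 to 5,000 and k of 12 or 21, the half-width grows by a factor of 1.39 to 2.27.

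**Step 3: type I error for a purely cluster-level factor.** If the naive standard error is too small by √DE, the true error of a nominal 5% test is 2 × (1 − Φ(1.96/√DE)). With 21 clusters this gives 13.4% at ICC 0.005 and 31.7% at ICC 0.02.

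**Step 4: simulation under the null.** An ordinary logistic model was compared with cluster-robust errors (N = 3,000, 12 or 20 equal clusters, 300 replicates). The ICC here is on the latent scale, so it agrees with Step 3 only approximately.

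| Latent ICC | Naive test, cluster-level factor (12 / 20 clusters) | Robust test, cluster-level factor (12 / 20) | Naive test, within-cluster factor (12 / 20) |
|---|---|---|---|
| 0.005 | 14.7% / 14.7% | 7.3% / 9.3% | 5.0% / 5.0% |
| 0.02 | 36.3% / 25.3% | 9.0% / 7.7% | 5.3% / 5.0% |
| 0.05 | 51.3% / 45.7% | 12.7% / 5.7% | 3.3% / 3.7% |

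With 300 replicates, the Monte Carlo standard error at a true 5% is √(0.05 × 0.95/300) = 1.3 points. The within-cluster results are therefore compatible with the nominal level; their robust-to-naive standard error ratio was 0.97 to 1.01. Plain robust errors remove most of the inflation but stay somewhat liberal with so few clusters.

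**The case against.** The strongest reply is that the article never says records are treated as independent. Naming PROC GENMOD does not imply it: that procedure fits generalized estimating equations through its REPEATED statement, and an article commonly leaves the correlation structure to a fuller document. This stands. A reader might infer that an independence analysis is planned, but the text does not support that reading. What remains is that REPEATED needs a subject variable and none is listed.

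A reader might also infer that a clustered analysis is ruled out for good. That goes too far. An operation number is collected, and control-center data are joined to each record after primary collection closes, so the missing code may still be obtainable. The article does not, however, name the operation number as the linkage key or say that the control center holds the vehicle for each operation. The anonymity statement protects individuals and does not exclude a vehicle or station code.

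Nor can it be said that the planned descriptive work yields intervals that are too narrow. PROC SQL is assigned only counts, rates and percentages, and clustering does not make a computed percentage wrong.

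Finally, gender, age and operation time can all vary within an ambulance and are little exposed. This is an exploratory pilot with case-based crew training and explained questionnaire terms, which may keep the ICC low. These points limit the size of the problem but do not supply the missing identifier.

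**Conclusion.** The concern holds as a gap in the data specification. Operations are clustered by ambulance, station and crew, and the listed fields contain no identifier for any of these, so as specified the regression models cannot account for the clustering.

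The harm is conditional on a positive ICC and on intervals or tests being reported. It falls on any interval for the main percentage and on factors that vary mainly between stations, plausibly operation area. Under the stated assumptions with 21 clusters, the half-width rises from 1.7 to between 2.2 and 4.8 points over ICC 0.005 to 0.05. False rejection for a purely cluster-level factor rises from 5% to about 15% at ICC 0.005 and 25% to 36% at ICC 0.02. Operation area would show less than this to the extent that ambulances work across area classes. The gap is worth closing because the study intends to report statistically significant factors and closing it costs little.

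**What to change.** - **Data.** Ask the control center to add a pseudonymised ambulance code (1 to 21) and station code (1 to 12) to the planned export, linked through the operation number. Confirm first that this number is the linkage key and that the vehicle is held per operation. Where more than one ambulance attended, state which code applies. The Ethical Considerations section requires committee approval of modifications, so seek it before the export.
- **Models.** Fit PROC GENMOD with a binomial distribution and REPEATED SUBJECT=ambulance, with station as the cluster in a sensitivity analysis. Use a small-sample-corrected sandwich variance, since plain robust errors were still liberal with 12 to 20 clusters. Name the SAS procedure or macro that supplies the correction.
- **Main percentage.** Compute any interval reported for it on a cluster basis, for example with the CLUSTER statement of PROC SURVEYFREQ.
- **Limitation.** State that ambulance and station capture rater clustering only in part, because the article does not say that crews stay with one vehicle or station and the form identifies no rater.

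The cost is one more export field, an ethics notification, a few lines of code and wider intervals. No crew member needs to be identified.

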### Ethical Considerations

The ethics committee of the University of Heidelberg revised and approved this study on May 30, 2023 (S-250/2023). The trial has been developed and will be executed according to all relevant national and international rules and regulations under the Declaration of Helsinki (2013 version) and International Council for Harmonisation Good Clinical Practice (E6, R2) guidelines. Consent from all participants will be obtained in the web-based form, and access to the questionnaire will be granted only after approval. Protocol modifications are not scheduled and are not foreseeable; if the need for them arises, they will have to be approved by the ethics committee. In case of modifications, a new study protocol will be released to all study participants via an official email. Due to the anonymous collection of data, participants do not have the choice to opt out after completing the questionnaire. Furthermore, as the questionnaire is anonymous, there is no possibility of inferring the identity of the participant or any other personal information. There is also no way to identify the personal data of patients using the secondary operational data provided by the control center. There is no compensation, financial or otherwise, provided to participants.

## Results

Data collection started as projected on September 18, 2023, and was ongoing until end of November 2023. We expect the documentation of several thousand rescue operations. We expect that many of these rescue operations will be unnecessary. Our intention is to train paramedics to give an immediate on-site evaluation of the correct care and treatment. We hope to identify patients’ reasons for calling a rescue coordination center so that we can give recommendations in advance on where to find the appropriate treatment options.

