**Results:**

Data collection started as projected on September 18, 2023, and was ongoing until end of November 2023. We expect the documentation of several thousand rescue operations. We expect the following study results: (1) many unnecessary rescue operations, (2) immediate on-site assessment of correct care and treatment, and (3) patients’ reasons for calling a rescue coordination center.

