### Design

The key feature of this exploratory, noninterventional, cross-sectional study is a web-based questionnaire (Table 1) for tablets or smartphones. In the first phase, each individual question on the web-based questionnaire was reviewed by an expert panel at the Department of General Medicine at Heidelberg University Hospital, and in the second phase, the questions were discussed with the heads of operations at the rescue coordination centers, as well as with selected paramedics. The focus was on the feasibility of this pilot study. When this study is rolled out (at large scale) there also will be analyses of interrater reliability.

**Table 1 table1:** Questionnaire for ambulance crews on emergency cases.

Item	Content
Operation number	(Free text)
Patient gender	Male Female Gender-diverse
Patient age group (years)	18-24 25-39 40-59 60-64 65-79 ≥80
Operation time on a weekend day or holiday^a^	Yes/no
Operation time during main opening hours of general practitioner care^b^	Yes/no
Classification of operation area (number of inhabitants)	Metropolitan (>100,000) Urban (30,000-100,000) Suburban (10,000-30,000) Rural (<10,000)
Working diagnosis	(Free text)
Treatment or procedure performed (multiple choices possible)	Being conveyed to a hospital Referral to a general practitioner or medical on-call service Continuance at home Patient refused being conveyed Therapeutic measures performed (Free text)
Appropriate treatment or procedure (multiple choices possible; no choice possible)	Being conveyed to a hospital autonomously Calling on the medical on-call service autonomously Consulting the general practitioner for further care Exclusively counseling Counseling by telephone possible Social caretakership Being conveyed by a patient transport ambulance (Free text)
Reasons for being conveyed to a hospital without medical indication (multiple choices possible; no choice possible)	Missed transportation opportunity by patient or relatives Patient insists on being conveyed by ambulance Social indication House call by general practitioner or medical on-call service indicated but not provided Medical on-call service not favored by patient Insecurity of team leader Language barrier (Free text)

^a^As defined by the state in which the operation took place.

^b^Main opening hours were defined as Monday, Tuesday, and Thursday from 7 AM to 7 PM, and Wednesday and Friday from 7 AM to 2 PM.

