The members of the expert panel determined which crucial dimensions of medical emergency treatments will be queried, including (1) working diagnosis, which is the assessment made on site by the ambulance crew with consideration of diagnostics that can be carried out preclinically; (2) procedures, including the ambulance crew’s approach to counseling, treatment, patient transport, and referral to other caregivers; (3) adequacy of care, that is, the assessment of the most suitable form of care, which is carried out by the ambulance crew based on the situation on site; and (4) problems that arise, that is, the evaluation of possible reasons why patients are not directed to the form of care that has been assessed as being most suitable.

The training of the paramedics consists of 5 vital elements. The important questions for assessing their concerns about possible rescue operations (Textbox 1) are described in in-person lectures. The five *W* questions are integrated in the questionnaire and special training is provided.

*W* questions and example cases.

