***W* questions**
Which typical use cases are presented?Who called? (Age and gender should be documented)Which concerns were stated? (Assessment of the emergency is an overarching goal of the study)When did the concerns occur? (Duration and assessment of the acute situation has to be included in the consideration)Where is the location? (Infrastructure, social environment, etc., should be documented)

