**Examples of possible rescue operation cases integrated into the training**
An ambulance is alerted with high priority because of high blood pressure and vertigo. On site, the crew can rule out current life-threatening conditions, only the blood pressure is slightly elevated beyond the patient’s known level after an upsetting argument a few hours before. Anamnesis brings out that the patient is familiar with vertigo and does not have any new kinds of symptoms. So, the ambulance crew cannot find any indication for conveyance at this moment and offers the patient to stay at home unless new kinds of symptoms or decline of general condition occur. The patient prefers to do so, but his daughter presses him to “have a thorough checkup in hospital” and does not concede. The patient is conveyed to the nearest hospital. After the operation, the ambulance crew fills in the questionnaire, describes their working diagnosis as “slightly elevated blood pressure without further symptoms, known vertigo without current worsening” and picks “hospital conveyance” as performed procedure, “consulting the GP in the further course” as appropriate procedure and “patient insists on conveyance by ambulance” (which includes relatives) as reason for hospital conveyance without urgent medical indication.An ambulance is alerted under the heading “attendance operation for fire brigade”. As there is no patient contact during the whole operation and therefore the operation is excluded from this study, the ambulance crew does not fill in the questionnaire.An ambulance and an emergency doctor’s car are alerted with high priority because of acute chest pain. On site, the medical examination shows evidence for an acute myocardial infarction and the patient is quickly treated and conveyed to hospital for further treatment. After terminating the operation, the ambulance crew fills in the web-based questionnaire with the items 1-9 only, because they categorize their treatment as appropriate.An ambulance is alerted with low priority because of a headache on a Saturday. On site, they find a young woman who is healthy except for a cold that has been lasting for “already six days” accompanied by a sinusitis and a feeling of pressure in her head. The symptoms didn’t change during the last days, and she was not satisfied by the advice of her GP and the request to await spontaneous recovery. The ambulance crew repeats the advice of the GP and recommends waiting and see and to contact the GP or alternatively the medical out-of-hours on-call service again if no improvement will occur. The patient insists on an immediate treatment, has never heard of the medical on-call service until now and claims not to be able to drive on her own, so the paramedics call the medical on-call service themselves and ask for a home call. After the operation, they fill in the web-based questionnaire, set their working diagnosis “headache associated with acute sinusitis”, pick “referral to GP or medical on-call service” and “continuance at home” as performed procedure, “consulting the GP in the further course” and “exclusively counseling” as well as “counseling telephonically possible” as appropriate procedures and select “missing transportation opportunities by patient and relatives” and add “patient didn’t know the medical on-call service” for reasons why the patient has not been directed to the appropriate caregiver straightforward.

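### Patients' reasons for calling are promised as a result, but only crew-judged reasons for non-indicated conveyance or missed suitable care are recorded, and the insistence option pools relatives with the patient

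*Protocol article*

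**What the plan says.** The Abstract (Results) gives patients' "reasons for calling a rescue coordination center" as the third of three expected results. The main Results section repeats this as a hope and attaches a use to it: "reasons for calling a rescue coordination center so that we can give recommendations in advance on where to find the appropriate treatment options". Under Data Management the article adds: "The free-text entries will be analyzed separately with qualitative methods to obtain a deeper insight into" what moves patients to act as they do.

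The instrument is Table 1, completed once per operation by the ambulance crew and representing the view of its most qualified member (Design). Its one item on reasons is headed "Reasons for being conveyed to a hospital without medical indication (multiple choices possible; no choice possible". Data Analysis names these conveyance reasons as one of the two main outcomes. Data Collection adds time of day, priority, keywords and a feedback code from the control center.

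In the first training case of Textbox 1, the crew suggests staying at home. "The patient prefers to do so, but his daughter presses him to" go to hospital for a checkup. The crew is shown choosing the option that the patient insists on conveyance, "which includes relatives) as reason for hospital conveyance without urgent medical indication".

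On the five W questions taught to crews, Design says that these "questions are integrated in the questionnaire and special training is provided". One of them reads "Who called? (Age and gender should be documented".

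**The concern.** Why someone calls and why that person ends up in hospital are different questions, put at different moments and often about different people. The first concerns a decision by a patient, relative or care home before any crew has arrived. The second concerns what happened after the crew had assessed the patient. Advice to the public on where to seek care, which the Results section wants to give, depends on the first. If the form captures only the second, one of three announced results cannot be delivered as worded, and conveyance reasons may be reported as though they were calling reasons.

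The insistence option raises a related problem within a main outcome. A table row that names the patient will be read as the patient's demand. If it also holds cases in which the patient wished to stay home and a relative pressed for transport, that reading is wrong for those cases, and the coded option cannot separate them afterwards.

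**Working it through.** No figure in the plan needs reproducing. The check sets what is promised beside everything that is collected.

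**1. The 10 items of Table 1.**
- Item 1: operation number (identifier).
- Items 2 and 3: patient gender and age group.
- Items 4 and 5: weekend or holiday; within GP opening hours.
- Item 6: operation area.
- Item 7: working diagnosis, as assessed by the crew.
- Item 8: what was done.
- Item 9: what would have been appropriate.
- Item 10: reasons for conveyance without indication.

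Items recording why the call was made: 0 of 10. Items recording who called: 0 of 10. Items answered by a patient or caller: 0 of 10. Items asking for any reason: 1 of 10 (item 10).

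**2. The 4 linked variables.** Time, priority, keywords and feedback code. The Aim section describes the priority and content of the alert as set by the dispatcher. None is described as recording the caller's reason: 0 of 4, so 0 of 10 + 4 = 14 fields in all.

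**3. What item 10 measures.** Its label restricts it to conveyance. The expert panel's fourth dimension (Design) is wider: the crew's evaluation of why a patient was not directed to the most suitable care. The fourth training case uses it in that wider sense, for a patient who stays at home. On either reading it is a crew judgement about what followed the call. In the third training case, where care was appropriate, the crew stops at item 9, so no reason of any kind is recorded for such operations.

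**4. The protocol's own list of calling reasons.** The Introduction names ignorance of the care structures, the patient's own sense of urgency and the need for safety as reasons why the ambulance service is alerted in nonurgent cases. None of these is a fixed option of item 10. They can appear only if a crew happens to write them as free text.

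**5. The insistence option.** Table 1 names the patient alone, and no option exists for insistence by a relative. In the first training case the patient's preference is to stay home and the pressure comes from the daughter, yet the case is filed under this option. The category is therefore patient or relative by instruction. The documents give no basis for estimating the share of each.

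**6. The W questions.** Age, gender and operation area have fields, and the working diagnosis touches on the concerns stated. The caller has no field. The statement that the W questions are built into the form is therefore not correct for this one.

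**The case against.** The strongest reply is that the crew's perspective is the declared design. The Abstract's Conclusions and the Aim both rest on paramedics' assessments, and the Discussion presents the study as complementing earlier work done through patients' eyes. Not asking patients is thus a choice, not an oversight. Both main outcomes in Data Analysis have matching items, and the Results section introduces calling reasons only as a hope. This stands, and it limits the point to a mismatch between a stated result and the instrument. It does not remove the mismatch, because the Abstract lists calling reasons as an expected result.

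A reader might go further and infer that nothing collected bears on motives. The documents do not support that. Crews can record that the patient did not favor the on-call service, lacked transport or faced a language barrier. In the fourth training case the free text notes that the patient had never heard of the on-call service. This information is indirect and crew-reported, but useful.

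A reader might also infer from "Who called? (Age and gender should be documented" that age and gender will be entered for the caller and so corrupt the regression covariates. Table 1 labels both fields as the patient's, Data Analysis uses them as such, and the form has no caller field. That error is conjecture. The missing field for symptom duration is also a weak complaint, since Textbox 1 asks only that duration be considered.

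Finally, the pooling of relatives with the patient is openly stated in the training text. It is a declared definition, not a hidden miscoding. It still does not match the label in Table 1, which is what a reader of the results would see.

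**Conclusion.** The point holds as a mismatch between claim and measurement. One of three expected results, patients' reasons for calling, has no dedicated field among the 14 collected and no patient or caller as respondent. What can be reported is the crew's view of why patients were conveyed without indication or did not reach suitable care, with indirect information on motives. Separately, one category of a main outcome must be read as insistence by patient or relative. How much of it comes from relatives is unknown, and nothing in the documents shows that it will be the most frequent reason.

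The number and percentage of inappropriate calls are not touched by this. The conclusion assumes that Table 1 and the list in Data Collection are the complete set of fields, as the article presents them.

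**What to change.** For this pilot, where collection ran to the end of November 2023, four changes of wording suffice:

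1. In the Abstract and Results, restate the third expected result as crew-perceived reasons for conveyance without medical indication or for not reaching suitable care.
2. Under Data Management, describe the free-text analysis as giving crew-reported, indirect information on patients' motives.
3. In tables and text, report the insistence category as patient or relative insisting.
4. Under Design, correct the statement that the W questions are integrated, noting that the caller is not recorded.

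These cost a few sentences and a narrower claim; no data or analysis changes.

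For the large-scale roll-out foreseen under Design only: add a field for who called and one for the stated reason for the call, and split insistence into patient and relative. The cost is a few extra entries per operation.
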